**12. Statistical Analysis**

The statistical analysis for this study will be conducted using the Statistical Package for the Social Sciences (SPSS; Chicago, IL, USA), version 25, with statistical significance set at p<0.05p < 0.05p<0.05.

Descriptive Analysis

The baseline characteristics of the participants across the three groups—Control Group (CG), Digital Video-Based Learning Group (DVBLG), and Traditional Educational Session Group (TESG)—will be summarized using descriptive statistics. For continuous variables, such as age and years of experience, we will calculate the mean and standard deviation (SD). For categorical variables, such as gender and prior pesticide training, frequencies and percentages will be presented.

Baseline Comparison

To confirm the comparability of the groups before the intervention, baseline characteristics will be assessed using a one-way analysis of variance (ANOVA) across the three groups, ensuring no significant differences could affect outcome interpretation.

Primary Outcome Analysis (Per-Protocol)

A per-protocol approach will be applied to analyze the primary outcomes, which include knowledge of pesticide safety, interpretation of pesticide labels, and understanding of the environmental impacts of pesticide misuse. The analysis will proceed as follows:

- Within-Group Changes: Paired t-tests will assess changes from baseline to post-intervention for each group.
- Between-Group Differences: A one-way ANOVA will compare differences between the groups in post-intervention scores. If significant differences are detected, post hoc tests (e.g., Tukey’s HSD) will be conducted to explore pairwise comparisons between groups.

Secondary Outcome Analysis

For secondary outcomes, including PPE usage and pesticide-handling practices, changes within each group will be assessed using paired t-tests, while differences between groups will be analyzed using one-way ANOVA with post hoc tests for further analysis as needed.

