**Study Arms**:

1. **Control Group (CG)**: Farmers will receive no intervention.
2. **Traditional Educational Session Group (TESG)**: Farmers will attend an in-person educational session on pesticide safety, health impacts, and label interpretation.
3. **Digital Video-Based Learning Group (DVBLG)**: Farmers will receive a 4-minute educational video via WhatsApp containing the same content as the in-person session.

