**Randomization**

Participants will be randomly assigned to one of three groups: the Control Group, the Digital Video-Based Learning Group (DVBLG), and the Traditional Educational Session Group (TESG). Each participant’s phone number will serve as their unique identifier, simplifying group allocation and follow-up communication without requiring participants to remember a specific code. To ensure a random allocation, we will use the RAND function in Microsoft Excel.

The process will be as follows:

1. Each participant’s phone number will be entered in a single column in Excel. The RAND function will generate a random number for each participant. These random numbers will then be used to sort the list of participants in ascending order, resulting in a randomized list.
2. Based on this sorted list, participants will be allocated sequentially to each of the three groups, ensuring equal distribution.
3. To facilitate communication, we will create a WhatsApp group for each team. We will use the group to invite the TESG to the educational session, send the educational video to the DVBLG, and provide them with instructions to watch it. Additionally, we will use the group to call them for the post-assessment.

This approach will ensure a transparent and unbiased randomization process, allowing us to assess intervention effectiveness across comparable groups.

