**6. Sample Size Calculation**

The sample size calculation for this randomized controlled trial will be based on prior data from a cross-sectional study conducted in the same region, which found that only 4% of farmers routinely read pesticide labels before preparing pesticide mixtures. To achieve a statistically meaningful improvement with our educational intervention, we aim to detect an increase in this behavior by 25%—raising it from 4% to 29%.

Using a significance level of 0.05 and a power of 80%, we estimate that each group (Digital Video-Based Learning Group, Traditional Educational Session Group, and Control Group) will require approximately 35 participants, totaling 105 participants across the three groups. However, we plan to recruit additional participants to account for potential attrition and ensure a robust final sample. The number of these additional participants will be determined based on observed participation and retention rates during the recruitment phase, allowing us to meet our target sample size despite potential dropouts. This approach will help maintain sufficient statistical power throughout the study, even if some participants cannot complete all stages.

7. **Description of the interventions.**

This randomized controlled trial will involve three distinct groups, each receiving different levels of intervention:

1. **Control Group (CG)**
   Participants in the control group will receive no educational intervention and will serve as a baseline to compare the effects of the other interventions. This group will only participate in baseline and follow-up assessments to measure changes in knowledge, practices, and understanding of pesticide labels without external educational support.
2. **Digital Video-Based Learning Group (DVBLG)**

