   The participants in this group will receive a 4-minute educational video on pesticide safety distributed via WhatsApp. The video will cover essential topics on pesticide use, focusing on reading pesticide labels, understanding FAO pictograms, interpreting color codes, and practicing safe handling procedures, including using personal protective equipment (PPE). Visual aids and examples will be incorporated into the video to enhance comprehension, and the content will be presented in Arabic to ensure clarity and accessibility. The video will be available for rewatching, allowing flexible, self-paced learning. Participants in this group will receive a transportation fee as an incentive for participating.
3. **Traditional Educational Session Group (TESG)**
   Participants in the traditional educational session group will attend an in-person, interactive training session. This session, led by the primary researcher with support from a plant protection specialist and an environmental health professor, will use PowerPoint presentations and encourage group discussions. Topics covered will mirror those in the video, including pesticide safety, label interpretation, pictograms, color coding, and PPE usage. The face-to-face format will allow for immediate questions, personalized guidance, and opportunities for farmers to share their experiences. The session will take place in the Safadi Foundation’s conference room in Der Dalloum, Akkar, with participants receiving transportation fees and breakfast as incentives.

Each intervention is designed to improve the participants' knowledge, practices, and interpretation of pesticide safety labels, with the goal of assessing which format—digital or traditional—is more effective in a resource-limited setting. The interventions are specifically crafted to address language and literacy barriers, ensuring accessible and practical education for the farmers involved.

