**12. Handling Missing Data**

Given the face-to-face interview method used to facilitate data entry through Google Docs, missing data is expected to be minimal. However, list-wise deletion will be applied to any remaining incomplete cases to ensure consistency across analyses. This strategy is intended to maintain accuracy while minimizing the impact of missing values on overall findings.

This approach will comprehensively assess intervention effectiveness across comparable groups, consistent with the analysis of the detailed results.

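### Per-protocol is the only analysis of the primary outcomes and its set is undefined; exclusion for non-adherence can fall only on the two active arms

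*Protocol*

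**What the plan says.** Section 12, Statistical Analysis, names the approach in a sub-heading and again in the text: "A per-protocol approach will be applied to analyze the primary outcomes". No as-randomised or intention-to-treat analysis appears anywhere in the protocol, even as a sensitivity analysis, and no criterion for the per-protocol set is given. The between-group test is stated as "A one-way ANOVA will compare differences between the groups in post-intervention scores", followed by post hoc pairwise tests such as Tukey's HSD. Baseline score does not enter it.

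The arms differ in what there is to adhere to:
- Control (Study Arms): "Farmers will receive no intervention". The description of the interventions adds: "This group will only participate in baseline and follow-up assessments".
- TESG (description of the interventions): "Participants in the traditional educational session group will attend an in-person, interactive training session".
- DVBLG (Randomization): the investigators will "send the educational video to the DVBLG, and provide them with instructions to watch it". No record of viewing is planned.

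The missing-data section says that "list-wise deletion will be applied to any remaining incomplete cases to ensure consistency across analyses". The sample size section says that "we plan to recruit additional participants to account for potential attrition", but gives no rate for dropout or non-adherence.

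**The concern.** Randomisation makes the three groups comparable as allocated. A per-protocol set keeps only those who did what their arm required. Here one arm requires a trip to a session, one requires watching a video, and one requires nothing beyond the two interviews. If farmers who skip the session are less motivated or less literate, removing them raises the TESG mean, while their counterparts among the controls stay in. The difference from control then mixes the effect of the teaching with the effect of the selection.

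Video versus in-person is affected too, because attending and watching need not select the same people. The Introduction presents WhatsApp as a way to reach dispersed farmers with few resources, so failing to attend or watch is part of what the trial should measure. Because set membership is undefined, it could also be settled after outcomes are known. More farmers would not remove the bias.

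**Working it through.** **The plan's own figure.** For 4% v 29%, two-sided alpha 0.05 (sidedness is not stated; two-sided assumed), 80% power and pooled variance under the null:

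n = [1.96 × √(2 × 0.165 × 0.835) + 0.8416 × √(0.04 × 0.96 + 0.29 × 0.71)]² / 0.25² = 33.4, so 34 per group.

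This agrees with the stated figure of about 35 (power at 35 is 81.9%). No number in the plan is disputed; the point concerns the analysis set.

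**Who can be excluded for non-adherence**

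| Arm | Requirement | Can non-adherence be observed as planned? |
| --- | --- | --- |
| Control | None beyond the two assessments | No intervention to adhere to |
| TESG | Attend one session | Yes, by attendance |
| DVBLG | Watch the video | No measure of viewing planned |

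**Size of the bias (illustration).** Assume no true effect, scores with SD 1, a fraction d excluded from one active arm and none from control, and a correlation ρ between the propensity to adhere and the post-intervention score. With z = Φ⁻¹(d) and λ = φ(z)/(1 − d):

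- bias in the arm mean = ρλ
- variance of the retained scores v = 1 + ρ²(zλ − λ²)
- SE of the difference = √(1/44 + v/[44(1 − d)]), with 133/3 ≈ 44 per arm
- false-positive rate = 1 − Φ(1.96 − bias/SE) + Φ(−1.96 − bias/SE)

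Example, d = 0.30 and ρ = 0.5: z = −0.524, λ = 0.497, bias = 0.248, v = 0.873, SE = 0.226, bias/SE = 1.10, false-positive rate 19.6%.

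| Excluded (assumed) | Bias in SD, ρ = 0.2 to 0.5 | False-positive rate of one two-sided 5% pairwise test |
| --- | --- | --- |
| 5% | 0.02 to 0.05 | 5.1% to 5.7% |
| 10% | 0.04 to 0.10 | 5.4% to 7.4% |
| 20% | 0.07 to 0.18 | 6.1% to 12.5% |
| 30% | 0.10 to 0.25 | 7.1% to 19.6% |

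The last column is for a single unadjusted comparison, not for Tukey's HSD.

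**What an as-randomised analysis costs.** If non-adherers gain nothing, the 29% becomes 0.04 + 0.25(1 − d):

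| Non-adherence (assumed) | Diluted rate | Needed per arm (80% power) | Power at 44 per arm |
| --- | --- | --- | --- |
| 0% | 29.0% | 34 | 89.9% |
| 10% | 26.5% | 39 | 84.8% |
| 20% | 24.0% | 47 | 78.1% |
| 30% | 21.5% | 56 | 69.8% |

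**The case against.** **The hypothesis is one of similarity.** The video is expected to work as well as the session, and as-randomised dilution can make two arms look alike. A per-protocol set has a proper role there. That stands, but it supports a per-protocol analysis beside an as-randomised one, not alone. The protocol sets no margin, uses difference tests and includes an untreated control, and for the contrasts with that control per-protocol is not the cautious choice.

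**Exclusions may be few.** There is one session, with transport fees and breakfast, and a four-minute video that can be watched again. That is fair: at 5% exclusion the bias is small.

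**Viewing is not measured.** If non-viewers cannot be identified, they cannot be removed, and the video-versus-control contrast may carry no adherence selection. This also stands. A reader might picture the video arm as self-reported viewers, but no self-report of viewing is planned. The case is clearest for TESG.

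**Controls can be lost too.** A control who misses the post-assessment drops out under list-wise deletion. That is correct, but it is loss to follow-up, which can affect all arms, and not exclusion for non-adherence.

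**Attrition and missing data.** Against the 105 required, the 133 or 150 farmers named elsewhere leave 21% (1 − 105/133) or 30% (1 − 105/150). A reader might take this as expected loss that contradicts the claim of minimal missing data. It is headroom: no dropout rate is stated, and the missing-data section most naturally refers to incomplete answers at interview. Nor can the share of farmers lost to list-wise deletion be worked out, because neither the number of questionnaire items nor an item-missing rate is given.

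**Conclusion.** The point holds for the choice of analysis set. Per-protocol is fixed as the sole analysis of the primary outcomes, its membership is undefined, and adherence-based exclusion can act only on the active arms. Following the plan as written risks selection bias in every primary between-group contrast, and the unadjusted ANOVA gives no protection. Bias in favour of the interventions is likely against control, most clearly for TESG, but not certain; for video versus in-person the direction is unknown.

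The size rests on assumed non-adherence and on an assumed link between adherence and score. It runs from negligible (0.02 SD at 5% exclusion, ρ = 0.2) to serious (0.25 SD at 30%, ρ = 0.5).

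It would go too far to say that the randomisation is discarded. Allocation remains random; it is the compared subsets, chosen afterwards, that lose its protection.

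**What to change.** In section 12, Statistical Analysis:
- Make the primary analysis as-randomised: every randomised farmer in the allocated arm, whether or not they attended or watched, with the post-assessment sought from all.
- Keep per-protocol as a supporting analysis, with its set defined in advance, including how attendance and viewing are established. Require the two analyses to agree before the video is called as effective as the session.

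In Handling Missing Data:
- Analyse each outcome on all farmers who have that outcome, instead of deleting any incomplete case from all analyses.
- Report loss by arm.

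The work is mostly wording. The Randomization section already uses the WhatsApp groups to call participants for the post-assessment, so non-attenders and non-viewers can be reached the same way. The denominator will vary between outcomes and must be shown. The real cost is that the estimated effect may be smaller and power lower: at 44 per arm it falls below 80% on the planning endpoint by 20% non-adherence if non-adherers gain nothing. The sample size section should allow for this.

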**10. Outcomes**

**Primary Outcome Measures**:

- Ability to correctly identify and interpret FAO pictograms on pesticide labels.
- Knowledge of health risks associated with pesticide use.
- Understanding of the environmental consequences of pesticide misuse.

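### Three primary outcomes share one unadjusted p<0.05 threshold; if any one may be reported as a primary result, the false-positive chance is about 8–14%, not 5%

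*Protocol*

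**What the plan says.** - Protocol section 10, Primary Outcome Measures, lists three items without ranking them: "Ability to correctly identify and interpret FAO pictograms on pesticide labels", "Knowledge of health risks associated with pesticide use" and "Understanding of the environmental consequences of pesticide misuse".
- Section 12, Primary Outcome Analysis, again gives three: "the primary outcomes, which include knowledge of pesticide safety, interpretation of pesticide labels, and understanding of the environmental impacts of pesticide misuse".
- Section 12 opens "with statistical significance set at" p<0.05. This one level covers the whole analysis and is not divided between outcomes.
- The between-group test is fixed: "A one-way ANOVA will compare differences between the groups in post-intervention scores". If it is significant, post hoc pairwise comparisons follow, with Tukey's HSD given as an example.
- Section 6 (Sample Size Calculation) uses the full 0.05 and 80% power on a single endpoint, routine label reading (4% to 29%). That endpoint is not among the three primary outcomes.

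No section names a lead outcome, a composite, a requirement that all three succeed, a testing order or a split of the 0.05.

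**The concern.** A 5% level describes one test. With three primary outcomes each compared with 0.05, the chance that at least one is significant by luck is above 5%. Tukey's HSD does not address this, because it adjusts for the three pairwise arm comparisons inside one outcome and leaves the number of outcomes untouched.

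The practical risk is a split result. Suppose label interpretation differs between arms at p=0.03 and the two knowledge outcomes do not differ. Under the protocol this can be reported as a significant primary finding at 5%, although the error rate behind that statement is higher. With no order or adjustment fixed in advance, which outcome leads the report can also be chosen after the data are seen.

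**Working it through.** **Inputs.** Three primary outcomes (sections 10 and 12); 0.05 per test (section 12); three arms of equal size (section 4, Randomization). Arm size is 35 from section 6, or 133/3 ≈ 44 from the number to be randomized in section 5. The recruitment text in section 5 gives 150, but the error rate hardly depends on arm size. The correlation between outcomes is not stated, so it is varied as an assumption.

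**1. The plan's own figure.** The protocol states no error rate across outcomes. Its one calculation, 4% against 29%, can be checked (two-sided, pooled variance, no continuity correction; the protocol does not state sidedness):

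n = [1.960·√(2·0.165·0.835) + 0.842·√(0.04·0.96 + 0.29·0.71)]² / 0.25² = 33.4, so 34 per arm.

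The stated 35 is consistent with this, and power at 35 is 81.9%. The calculation therefore spends the full 0.05 on one test and leaves nothing for several primary tests.

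**2. Independent outcomes.** 1 − 0.95³ = 0.143, or 14.3%.

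**3. Correlated outcomes.** Simulation with no true difference: three arms, three normally distributed outcomes with equal pairwise correlation r, one ANOVA per outcome at 0.05, 80,000 trials per setting. Chance of at least one significant ANOVA:

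| r (assumed) | 35 per arm | 44 per arm |
|---|---|---|
| 0 | 14.2% | 14.2% |
| 0.3 | 13.7% | 13.6% |
| 0.5 | 12.6% | 12.7% |
| 0.7 | 11.3% | 11.2% |
| 0.8 | 10.0% | 10.0% |
| 0.9 | 8.6% | 8.5% |

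Each ANOVA alone stayed at about 5%, so the excess comes from having three of them.

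**4. If one outcome truly differs.** Two true nulls remain: 1 − 0.95² = 9.75% for independent outcomes.

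**5. After adjustment.** When nothing truly differs, Holm makes a false claim only if the smallest p-value is below 0.05/3 = 0.0167. For independent outcomes that is 1 − (1 − 0.0167)³ = 4.9%; simulated over r = 0 to 0.9 at 44 per arm, it is 4.9% down to 3.0%.

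**6. Power cost of Holm.** For a test with 80% power at 0.05, power at 0.0167 is Φ(1.960 + 0.842 − 2.394) = Φ(0.408) = 0.658. This is a normal approximation. The same step for a three-arm F test with 44 per arm (non-centrality set to give 80% at 0.05) gives 65.6%. On the protocol's own 4% against 29%, the formula in step 1 with 2.394 in place of 1.960 gives 44.8, so 45 per arm, and power at 44 per arm is 79.2%. That last figure concerns label reading; the protocol has no design figures for the three listed outcomes.

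**The case against.** The strongest reply is that this is largely a gap. Rules for combining outcomes are often left to a statistical analysis plan, none is shown, and a general p<0.05 threshold does not exclude such a rule. Part of this stands: the protocol never says that one significant outcome makes the trial positive, so the inflated rate must be stated conditionally. But the point does not rest on the gap alone. The protocol itself fixes three primary outcomes, the test, the post hoc method and the level, and that combination, followed as written, exceeds its stated 5%.

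A second reply concerns correlation. All three outcomes come from one questionnaire administered by the same surveyors (section 8), so high correlation cannot be ruled out. This stands too, which is why the range goes down to about 8% rather than stopping at 11%. It remains above 5% throughout.

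A third reply is that one ANOVA per outcome is inferred. It is the natural reading of section 12, but no sentence says so.

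A reader might also go further and argue that, because the hypothesis is that the video is as effective as the session, all three tests must succeed, so joint power falls below 80%. The documents do not support this. The ANOVAs test for differences, and significant differences among three arms do not show that video and session are equally effective. Nor does the protocol give a power figure for any of the three primary outcomes.

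**Conclusion.** The point holds in conditional form. If any one significant outcome may be reported as a primary result, which the protocol allows, the chance of at least one false primary result when there is no true effect is about 8–14% rather than 5%. This rests on one ANOVA per outcome, no true effect on any outcome, and assumed correlations between 0 and 0.9. The nine within-group paired t-tests on primary outcomes (three arms by three outcomes) are not counted.

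A reader might infer that the trial's error rate simply is 11–14%. That is too strong: it presumes a rule that any one outcome suffices, which the protocol does not state, and correlations no higher than about 0.7. If all three outcomes had to be significant, there would be no inflation, but the protocol does not state that rule either.

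The change should be made. The problem does not invalidate the trial, and wording settles it.

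**What to change.** Amend sections 10 and 12 in one of two ways.

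- **One primary outcome.** For example, name interpretation of FAO pictograms, the listed outcome closest to the label interpretation in the primary objective. That objective does not mention pictograms and also covers safety practices, so the choice is the sponsor's to justify. Test the other two outcomes afterwards in a stated fixed order, each at 0.05 and only if the one before is significant. Cost: an outcome later in the order cannot be claimed once an earlier one fails.
- **Three primary outcomes with Holm.** Order the three omnibus ANOVA p-values from smallest to largest and compare them with 0.0167, 0.025 and 0.05, stopping at the first that fails. Cost: a test with 80% power at 0.05 has about 66% at the strictest step.

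Under either option, say that the rule governs claims of a difference between arms on the individual outcomes. It should not be presented as the basis for a claim that video and session are equally effective. Neither option requires a change in data collection.

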**11. Data Collection**

Data will be collected at two time points through face to face interview:

1. Baseline Assessment: Before the intervention, all participants will complete a structured questionnaire assessing their knowledge, practices, and understanding of pesticide safety labels.
2. Post-Intervention Assessment: Following the interventions, participants will complete a post-intervention questionnaire to measure changes in their knowledge and practices.

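### Baseline scores are collected from everyone, but the primary between-arm test leaves them out: a valid analysis that baseline adjustment would sharpen at no cost

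*Protocol*

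**What the plan says.** Protocol Section 11 (Data Collection) plans two face-to-face assessments. At the first, "Before the intervention, all participants will complete a structured questionnaire assessing their knowledge, practices, and understanding of pesticide safety labels". At the second, "participants will complete a post-intervention questionnaire to measure changes in their knowledge and practices".

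Protocol Section 12 (Statistical Analysis) gives two steps for the primary outcomes. Within arms: "Paired t-tests will assess changes from baseline to post-intervention for each group". Between arms: "A one-way ANOVA will compare differences between the groups in post-intervention scores", followed by post hoc pairwise tests, with Tukey's HSD as the example, if the overall test is significant.

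For the secondary outcomes, "changes within each group will be assessed using paired t-tests, while differences between groups will be analyzed using one-way ANOVA". This sentence does not say whether the ANOVA takes post-intervention or change scores.

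Under Baseline Comparison, "baseline characteristics will be assessed using a one-way analysis of variance (ANOVA) across the three groups", with the stated purpose of "ensuring no significant differences could affect outcome interpretation".

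The protocol contains no ANCOVA, no between-arm comparison of change scores and no group-by-time model.

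**The concern.** Three features of Section 12 belong together.

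- The primary between-arm test makes no use of the baseline value of the outcome, although Section 11 collects it from everyone. That value is usually the covariate most closely related to the post score, so precision is given up.
- The baseline significance test is given a task it cannot do. A non-significant result does not show that the arms are comparable, and no adjustment follows from either result.
- Change from baseline is tested only within each arm. Those tests are not randomised comparisons, and each absorbs any effect of being interviewed a second time. The control arm removes that effect only when arms are compared with each other.

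The stake is the contrast between video and in-person session. The Hypothesis section expects the two to be equally effective, and a claim of similarity is only as good as the interval around that contrast. The secondary objective also asks whether the video improves protective-equipment use without naming a comparator, so a within-arm p-value could be offered as the answer.

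**Working it through.** **The plan's own figure.** Section 6 gives about 35 per arm for 4% versus 29%, alpha 0.05 and 80% power. The pooled two-proportion formula (two-sided, no continuity correction) gives 33.4, so 34 per arm, which agrees. That calculation concerns a binary label-reading behaviour. It supplies neither an SD nor a baseline-to-post correlation for the scores analysed in Section 12.

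**Inputs.**
- Arm size: Section 5 randomises 133 in equal groups, 133/3 ≈ 44 per arm. The recruitment text in the same section gives 150, which would be 50 per arm. I use 44.
- Correlation r between baseline and post score: not in the protocol. Assumed 0.3, 0.5 and 0.7.
- Results are in units of the post-score SD, because no SD is given.

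**Precision of one pairwise contrast.**

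Post-only ANOVA, 95% half-width before Tukey adjustment: t(0.975, 129) × √(2/44) = 1.979 × 0.2132 = 0.42 SD.

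ANCOVA multiplies the variance by 1 − r², so the half-width is multiplied by √(1 − r²). The one lost degree of freedom is negligible here.

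| r (assumed) | Variance factor | Half-width | Equivalent post-only n per arm, 44/(1 − r²) |
|---|---|---|---|
| 0 (no adjustment) | 1 | 0.42 SD | 44 |
| 0.3 | 0.91 | 0.40 SD | 48 |
| 0.5 | 0.75 | 0.37 SD | 59 |
| 0.7 | 0.51 | 0.30 SD | 86 |

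**Chance imbalance.** If two arms happened to differ by 0.3 SD at baseline, the post-only difference would be shifted by 0.3 × r, that is 0.09, 0.15 or 0.21 SD at r = 0.3, 0.5 or 0.7. An imbalance of 0.3 SD is below the 0.42 SD that an unadjusted pairwise test needs for significance at this arm size, so a baseline test would often not flag it.

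**What the paired tests can show.** Let two arms have the same true gain d, in SDs of the change score. Let p be the power of one arm's paired t-test (noncentral t, 43 df, noncentrality d√44). The probability that exactly one of the two is significant is 2p(1 − p).

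| d | p | 2p(1 − p) |
|---|---|---|
| 0.3 | 0.494 | 50% |
| 0.5 | 0.900 | 18% |
| 0.6 | 0.973 | 5% |

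The quantity 2p(1 − p) cannot exceed 50%, so the first row is the worst case. The protocol states no expected score gain, so no row can be singled out as the likely one.

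**The case against.** The strongest reply is that this is a choice about efficiency, not an error. Under the randomisation described, ANOVA of post scores is unbiased and holds its type I error. Chance baseline imbalance is part of the sampling error that the standard error already covers. This stands in full. A reader might infer from the missing covariate that the planned comparison is invalid or biased; the protocol does not support that.

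A reader might also infer that the formats will be compared by asking which arm reached significance. The protocol does not say so. It provides a between-group test with pairwise follow-up, and the control arm is assessed at both time points. The within-arm tests carry a risk of misreading; they are not the plan's basis for comparing arms. The risk remains because they come first under the primary analysis and are given no descriptive-only status.

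The gain is also unknown. Low correlation cannot be excluded, since training may weaken the link between baseline and post scores, and at r = 0.3 the improvement is small. The disagreement probability also shrinks quickly as the true gain grows. Both points stand, and the ranges above reflect them.

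Finally, the post-only wording is explicit for the primary outcomes only. For the secondary outcomes the protocol leaves open which score enters the ANOVA, so the same criticism is not established there. Nor does Section 11 say outright that the two questionnaires are identical. The planned paired t-tests, however, already require the same score at both visits, and ANCOVA asks for no more.

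**Conclusion.** The point holds as a free improvement. The primary between-arm analysis is valid but sets aside baseline information that is being collected anyway. The saving in variance is 9%, 25% or 49% for an assumed r of 0.3, 0.5 or 0.7. It rests on that assumption, on about 44 per arm and on a linear relation between baseline and post score. The half-widths are before Tukey adjustment; if the same multiplier is used for both analyses, the relative gain is unchanged.

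Separately, whatever r is, significance in one arm and not in another is no evidence of a difference between formats, and a non-significant baseline test does not establish comparability. A SAP not seen here could add detail, but the protocol itself names the method, so the wording should be changed there.

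**What to change.** In Section 12, for each primary score, replace the post-only ANOVA by an ANCOVA of the post-intervention score on arm and the baseline value of the same score. Name no optional covariates, so that none can be chosen after the data are seen. Report adjusted differences with 95% confidence intervals and Tukey-adjusted pairwise contrasts.

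Report within-arm changes descriptively, not as evidence of effect. Do not rely on the baseline significance test to establish comparability; a descriptive baseline table is enough.

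For secondary outcomes, use the same baseline-adjusted model where the outcome is a numeric score and a baseline-adjusted logistic model where it is binary. This means stating which outcomes are of which kind.

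The cost is wording plus that classification. No further data are needed, and SPSS, the software already named, fits both models.
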